### Sample

2.2

Sample size was calculated using G*Power 3.1.9.7 software (41), considering a repeated measures ANOVA design with two groups (experimental *vs.* control) factors, and two measurement times (pre *vs.* post). The estimated minimum sample size at alpha 0.05 and statistical power of 80%, for moderate effect size (f = 0.25), was approximately 34 subjects (17 per group). At baseline, participants will be pre-screened using an online questionnaire to determine eligibility.

The inclusion criteria were: (i) minimum age of 18; (ii) at least one year of competitive football experience; (iii) no eye problems that impair vision; (iv) no history of neurological injuries; (v) abstinence of caffeine, alcohol and intense physical activities in the previous 24 h before each experimental session; (vi) having slept for at least 7 h the night before. On the other hand, the exclusion criteria were: history of neurological injury; uncorrected vision problems; diagnosis of psychological disorders; use of psychoactive substances in the last 24 h before the experimental sessions; any form of nystagmus for electrophysiological contraindications for electrophysiological recording. The operationalization and description criteria are summarized in Table 1.

**Table 1 T1:** Sample operationalization and description criteria.

Topic	Description	Operationalization
Age	Minimum age of 18 years	Participants aged 18 years or older. There is no maximum age limit stipulated in the protocol.
Gender	Gender balance	Sample of 24 men and 24 women, in equal number for experimental and control groups.
Competitive experience	Minimum of 1 year of competitive experience	Football players with a minimum of 1 year of regular practice in competitive condition
Health condition	No conditions preventing the practice of sport	Individuals with a history of neurological injuries, uncorrected visual problems, diagnosed psychological disorders, use of psychoactive substances in the last 24 h, or any clinical limitation to physical exertion will be excluded. Pregnant women will also be excluded.
Legal and ethical criteria	Compliance with current regulations	The study complies with the GDPR and the provisions of Decree-Law No. 5/2007, ensuring that all participants meet the legal and ethical conditions for physical exercise.

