To ensure data quality and reproducibility, EEG signals will undergo standardized pre-processing procedures. Data will be processed in MATLAB R2025a (MathWorks, Natick, MA, USA) using EEGLAB v2025. Continuous recordings will be visually inspected to identify gross artifacts or recording instabilities, and non-EEG channels will be removed prior to analysis. Signals will be band-pass filtered between 1 and 45 Hz using a zero-phase finite impulse response (FIR) filter and re-referenced to a common average reference. Artifact correction will be performed using Independent Component Analysis (extended infomax algorithm). Independent components will be automatically classified using the ICLabel plugin integrated in EEGLAB, and components identified as ocular, muscular, cardiac, line-noise, or other non-brain sources with high probability (≥0.90) will be removed prior to signal reconstruction. Channels exhibiting persistent excessive noise throughout the recording will be excluded from analysis. All preprocessing procedures will be applied consistently across participants and experimental conditions to ensure methodological standardization and internal validity.

Oculomotor activity will be recorded with the Pupil Core system (Pupil Labs GmbH, Germany), with sampling at 200 Hz. This equipment will allow the analysis of fixations, saccades, pupillary dilation or and blink rate, during the LSPT. The ETS was only applied in the LSPT, as it contains visual stimuli while performing gaze orientation and control of attention, appearing as especially appropriate to analyze gaze patterns (53). In addition, the LSPT is longer in duration, which makes it possible to collect consistent eye activity data. Vansteenkiste et al. (54) demonstrated a correlation between LSPT performance and gaze patterns in young players, reinforcing that this type of test is suitable for analyzing oculomotor metrics. In contrast, the Y-SART is a simple task and it presents brief visual stimuli, so the use of an eye-tracker is not justified. Recent research has demonstrated that motor skills (e.g., sprinting, changing direction, reactive strength) are the main determinant in performance on the Y-SART and is also affected by sensory/perceptual processes to a smaller extent or indirectly (55). The data will be processed with open-source software provided by the manufacturer.

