#### Cortical activity (EEG)

2.5.1

Cortical electrical activity will be measured with the EMOTIV EPOC Flex EEG device, in order to assess neurophysiological changes related to mental fatigue elicited by the ST. Validation studies have demonstrated that the Emotiv system is capable of recording physiologically meaningful EEG signals and event-related potentials comparable to laboratory systems, although with lower signal-to-noise ratio and reduced reliability compared to medical-grade devices (58, 59). These findings suggest that while suitable for non-critical research applications, limitations remain when high precision or maximal signal robustness is required.

The analysis will focus on the theta (4–7 Hz), alpha (8–13 Hz) and beta (13–30 Hz) frequency bands, with an emphasis on the frontal and parietal regions, traditionally linked through processes of executive control, sustained attention, sensory-motor integration and regulation of the mental load (19, 60–62).

Although increases in frontal theta power and decreases in parietal alpha power have frequently been reported in association with sustained cognitive effort and fatigue-related states, these oscillatory changes are not specific or exclusive markers of mental fatigue. Theta and alpha modulations are influenced by multiple cognitive and attentional processes, including task engagement, vigilance, motivational state, and general mental workload (19, 60, 61). In addition, alterations in beta activity have been associated with changes in cortical stability and motor-related activation (61, 62). Therefore, in the present protocol, changes in these frequency bands will be interpreted as neurophysiological correlates associated with cognitive load and fatigue-related states, rather than definitive biomarkers of mental fatigue.

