### Statistical analysis

2.6

All statistical analyses will be performed using IBM SPSS Statistics version 29.0 (IBM Corporation, Armonk, NY, USA), with a significance level set at 5% (*p* < 0.05). Descriptive statistics (mean, standard deviation, 95% confidence intervals, and range) will be calculated for all outcome variables, including EEG spectral powers, oculomotor parameters, motor performance scores, and subjective fatigue ratings. These data will be stratified by group (experimental and control) and time (pre- and post-intervention) and presented visually using box plots and line graphs to facilitate interpretation (88, 89).

To assess the effect of mental fatigue, paired t-tests will compare pre- and post-intervention results within each group, while independent t-tests will compare the experimental and control groups at each time point (88, 90). For EEG outcomes, repeated-measures ANOVA models will include Time (pre vs. post mental fatigue) and Recording Condition (eyes open, eyes closed, motor imagery) as within-subject factors, and Group (experimental vs. control) as a between-subject factor (88, 90). Assumptions of normality and sphericity will be evaluated prior to analysis, following established recommendations for repeated measures designs (88, 91). When sphericity is violated, the Greenhouse-Geisser correction will be applied. Effect sizes will be reported using eta squared (*η*^2^), interpreted according to Marôco (90) as small (<0.04), moderate (0.04–0.25), or large (≥0.25). Statistical power (π) will also be reported when applicable (92, 93).

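### The EEG repeated-measures ANOVA uses only participants with all six recording segments; a linear mixed model would keep the rest, with a gain that depends on how segments are lost

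*Protocol article*

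**What the plan says.** Section 2.3 describes a five-minute EEG recording split into eyes open, eyes closed and motor imagery. Section 2.4 repeats it after the intervention and the second round of motor tests. Section 2.6 analyses the result in SPSS: "repeated-measures ANOVA models will include Time (pre vs. post mental fatigue) and Recording Condition (eyes open, eyes closed, motor imagery) as within-subject factors", with Group as the between-subject factor. It adds checks of sphericity, the Greenhouse-Geisser correction and eta squared. A later paragraph of 2.6 speaks more loosely of repeated-measures models for the regions of interest, but names no likelihood-based model. Sections 2.5.1.1 and 2.6 call the predefined-region analyses primary.

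On data quality, section 2.5.1 concedes that the device has "lower signal-to-noise ratio and reduced reliability compared to medical-grade devices", and section 2.3 says: "Channels exhibiting persistent excessive noise throughout the recording will be excluded from analysis".

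On size, section 2.2 reports a calculation "considering a repeated measures ANOVA design with two groups" and "two measurement times". "The estimated minimum sample size" at 5% alpha and 80% power, "for moderate effect size (f = 0.25), was approximately 34 subjects (17 per group"). No allowance for loss is stated there. Table 1 in the same section gives 24 men and 24 women.

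**The concern.** Sphericity checks, Greenhouse-Geisser and eta squared mark the method as the classical ANOVA, which deletes listwise. Someone with five good segments and one bad one contributes nothing, not even to Group x Time, although the five carry information on it. Six chances to lose a person turn a small loss rate per segment into a larger loss of participants, and 34 was the smallest number that met the power target. At stake is the power of analyses that the article labels primary. If loss differed between groups after the Stroop task, the comparison itself could also be affected.

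**Working it through.** **Inputs.** From section 2.2: 2 groups, 2 times, f = 0.25, alpha 0.05, power 80%, N = 34. From sections 2.3, 2.4 and 2.6: 2 recordings x 3 conditions = 6 cells. Assumed, because the article does not state them: a correlation of 0.5 between pre and post, and the loss rates.

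**1. The plan's own figure.** For the Group x Time F test, lambda = f² x N x m / (1 - rho), with 1 and N - 2 degrees of freedom. With m = 2 and rho = 0.5, lambda = 0.0625 x 34 x 2 / 0.5 = 8.5, and power is 80.7%. At N = 33 it is 79.5%. So 34 is reproduced exactly and is the smallest N that reaches 80%. The equivalent standardised difference in change is d = 1.0, since d² x 17 / 2 = 8.5. The correlation matters: at N = 34, power is 51.6% for rho = 0, 66.6% for 0.3 and 95.4% for 0.7.

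**2. Power by number of complete cases (rho = 0.5).** 34: 80.7%; 33: 79.5%; 32: 78.1%; 31: 76.8%; 30: 75.3%; 28: 72.1%; 25: 66.8%.

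**3. Scattered loss.** If each segment is lost independently with probability q, the complete share is (1 - q)⁶. The last column is from simulation of a likelihood-based analysis with condition effects.

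| q | (1 - q)⁶ | Complete of 34 | Power, ANOVA | Power, all usable segments |
|---|---|---|---|---|
| 2% | 0.886 | 30 | 75% | about 80% |
| 5% | 0.735 | 25 | 67% | about 79% |
| 10% | 0.531 | 18 | 51% | 77-79% |

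The last column depends on the assumed split of variance between participants and segments. A cruder calculation on the mean change over matched segments, with segment noise supplying 10% to 100% of the variance, gave 78-81%, 73-81% and 67-80%. It beat listwise deletion throughout.

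**4. Whole-recording loss.** If a pre or post recording fails as a unit, the complete share is (1 - q)².

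| q per recording | (1 - q)² | Complete of 34 | Power, ANOVA |
|---|---|---|---|
| 2% | 0.960 | 33 | about 80% |
| 5% | 0.903 | 31 | about 76% |
| 10% | 0.810 | 28 | about 70% |

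Here a mixed model adds only about 0 to 3 points, because someone with no post recording says little about change.

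**5. If the target is 48.** Power with all 48 complete is 92.4%. Scattered loss of 5% leaves 48 x 0.735 = 35 complete, with power about 82%. Scattered loss of 10% leaves 48 x 0.531 = 25 to 26, with power about 67%.

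**The case against.** - **Loss may cluster.** Each recording is one sitting with one gel cap, so poor contact could spoil all three conditions together. This stands. It shrinks both the loss and the benefit of the remedy (step 4).
- **The cited text does not show segment loss.** The exclusion rule removes channels, outcomes are taken over regions of interest, and independent component analysis removes ocular and muscular components. The signal-to-noise remark gives no loss rate. This stands too: it makes loss less likely, and its size stays an assumption.
- **The 80% is not the power of this model.** It belongs to a two-group, two-time calculation that names no outcome and omits recording condition. Correct; the figures above show sensitivity at the design effect, not the EEG model's actual power.
- **Missing-data rules may sit in an analysis plan not shown.** True, and their absence is not the point. The point is the method that the article itself fixes.
- **Only EEG is affected.** Correct; the t-tests on the other outcomes keep the participant.

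Two stronger readings are tempting. A reader might infer that a single unusable segment forfeits the stated power, but one lost participant costs 1.2 points, and it takes about three to reach 76.8%. A reader might also infer that loss will be greater after the Stroop task and bias the result. Section 2.5.2.4 does expect more blinking with fatigue, but blinks are targeted by the artefact correction, and the article shows no differential loss.

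**Conclusion.** The point holds in a limited form. The EEG analysis as fixed is complete-case over six cells and discards usable data. With scattered loss of 2% to 10% per segment, the ANOVA gives about 75% down to 51% power, against about 80% down to 77-79% with all usable segments. With loss of whole recordings the two differ by only about 0 to 3 points. This rests on N = 34, d = 1.0 on the change, an assumed correlation of 0.5 and assumed loss rates. With 48 participants the shortfall largely recedes: power stays above 80% at 5% scattered loss, though not at 10%. The change is still worth making, because the mixed model does not do materially worse in any pattern examined and matches the ANOVA when data are complete.

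**What to change.** In section 2.6, replace the repeated-measures ANOVA for the EEG outcomes by a linear mixed model fitted by restricted maximum likelihood. Include Group, Time, Condition and their interactions as fixed effects, random effects for participant and participant-by-Time, and Satterthwaite or Kenward-Roger degrees of freedom. Include every usable segment from every randomised participant, and name Group x Time as the test of interest. Separately, reconcile the 34 in section 2.2 and the abstract with the 48 in Table 1.

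The cost is analysis wording only. The covariance structure must be fixed in advance, and eta squared is not given directly, so the effect-size sentence needs adjusting. The model removes bias only where loss depends on observed data. It would not cure loss driven by the unobserved signal itself.

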The statistical approach defined in this methodology and experimental protocol is structured to support the analysis of neurophysiological, visual, motor, and subjective outcomes using established quantitative methods. Descriptive statistics will characterize each variable, while paired and independent t-tests will assess intra- and intergroup differences before and after the intervention. A repeated measures ANOVA will be used to examine the effects of time and group interaction, with assumptions of normality and sphericity tested to ensure validity. Effect sizes (*η*^2^) and test power (π) will be reported to improve the interpretability and generalization of the results, following Marôco (90), Pallant (89), and Field (88). Pearson's correlation will be used to explore associations between domains (e.g., EEG activity and motor performance), interpreted according to Marôco (90). When appropriate, ANCOVA will control for individual variability, such as age or training experience. This analytical framework supports the protocol's goal of detecting the effects of mental fatigue on various dimensions of performance, based on robust methodological and statistical criteria.

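### The plan reports test power (π) beside the estimated effect sizes to aid interpretation; read naturally, this is observed power, which only restates the p-value

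*Protocol article*

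**What the plan says.** Section 2.6 (Statistical analysis) sets out the t-tests and the repeated-measures ANOVA, says that eta squared will be reported, and adds: "Statistical power (π) will also be reported when applicable". The software is fixed: "All statistical analyses will be performed using IBM SPSS Statistics version 29.0". Section 3 (Discussion) returns to the subject and gives the purpose: "test power (π) will be reported to improve the interpretability and generalization of the results".

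The planning power is given separately, in section 2.2 (Sample): "The estimated minimum sample size at alpha 0.05 and statistical power of 80%, for moderate effect size (f = 0.25), was approximately 34 subjects".

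Neither section 2.6 nor section 3 says whether π is observed or a priori power, or names an effect size at which it is to be calculated. The 95% confidence intervals in section 2.6 are listed with the descriptive statistics, by group and time point.

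**The concern.** Power belongs to a design at a stated true effect. If the estimated effect is put in its place after the analysis, the result is a transformation of the test statistic, and therefore of the p-value. A reader who sees p = 0.20 and a power of 25% has been told one thing twice, but may take the second figure as evidence about the design.

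What is at stake is how results are read, null results above all. There are many outcomes across EEG, gaze, LSPT, Y-SART and VAS, so some null results are likely. Sections 2.5.6 and 3 also plan to read preserved performance as a possible compensatory response. That reading depends on whether the data rule out a meaningful decrement. Observed power cannot show this, because it is low for every non-significant result and rises only as the p-value falls.

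**Working it through.** **Inputs from the protocol article.** Two groups by two times, f = 0.25, alpha 0.05, power 80%, N = 34 with 17 per group (section 2.2); SPSS, 5% level, three recording conditions in the EEG model (section 2.6). Table 1 gives 24 men and 24 women, which conflicts with 34; N = 48 is used as a sensitivity check.

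**Assumption.** The document gives no pre-post correlation ρ. The value 0.5 is used, with 0.3 and 0.7 as a range.

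**Step 1. Reproduce the planned sample size.** For the Group x Time interaction with m = 2 times, the noncentrality is λ = f² × N × m / (1 − ρ), with 1 and N − 2 df.

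At ρ = 0.5: λ = 0.0625 × 34 × 2 / 0.5 = 8.5. The critical value is F(1, 32) = 4.149 and the power is 80.7%. The smallest even N that reaches 80% is 34, as stated. At ρ = 0.3 it would be 46, and at ρ = 0.7 it would be 22.

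**Step 2. Observed power as a function of p.** The observed-power calculation uses λ = df1 × F_obs. Observed power is the probability that a noncentral F with that λ exceeds the critical value. With the degrees of freedom and alpha fixed, F_obs is determined by p, so observed power is too. For Group x Time with 1 and 32 df:

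| p | F_obs | Observed power |
|---|---|---|
| 0.01 | 7.499 | 75.7% |
| 0.05 | 4.149 | 50.6% |
| 0.10 | 2.869 | 37.6% |
| 0.20 | 1.712 | 24.6% |
| 0.50 | 0.465 | 10.2% |

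The printed value reaches 80% only when p is about 0.007.

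**Step 3. Upper limit for a non-significant result (value at p = 0.05).**

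| Test | df | Limit |
|---|---|---|
| Group x Time, N = 34 | 1, 32 | 50.6% |
| Group x Time, N = 48 | 1, 46 | 50.4% |
| Paired test within a group of 17 | 16 | 51.3% |
| EEG terms with Recording Condition, N = 34 | 2, 64 | 58.3% |

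For the last row, a Greenhouse-Geisser epsilon between 0.5 and 1 gives a limit between 50.6% and 58.3%.

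**Step 4. Spread of the printed value when the planned effect is true (f = 0.25, N = 34, Group x Time).** F_obs follows a noncentral F with 1 and 32 df and the λ of step 1. Its 5th and 95th percentiles are converted as in step 2.

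| Assumed ρ | λ | True power | Printed value, 5th to 95th percentile |
|---|---|---|---|
| 0.3 | 6.07 | 67% | 0.13 to 0.99 |
| 0.5 | 8.5 | 80.7% | 0.23 to 0.997 |
| 0.7 | 14.17 | 95% | 0.52 to 1.00 |

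At ρ = 0.5, about 19% of trials (100 − 80.7) miss significance. Among these the median printed value is about 0.34 and none exceeds 0.506, although the design's power is 80.7% in every one of them.

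**The case against.** The strongest objection is that the plan never uses the word observed. If π were evaluated at the planned f = 0.25, the problem would not arise. This stands in part: the reading is an inference. It is well supported, since π is paired with the estimated effect size in both places, no other effect size is named, and the planning power already appears in section 2.2. Power at the planned effect is fixed before any data, so it could not help to interpret individual results. If something else is meant, the text has to say so.

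Three stronger readings are tempting and should not be made:

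- A reader might infer that every test will carry a power figure. Section 2.6 says only that this happens when applicable.
- A reader might apply the 51% limit to all results. It does not cover EEG terms with Recording Condition, where the limit is up to 58%. Section 2.6 names the Group factor in an ANOVA explicitly for EEG outcomes and describes t-tests in general terms, while section 3 describes a time-by-group ANOVA more broadly. The one-to-one relation with p holds in either case.
- A reader might infer that the investigators intend to dismiss null results as underpowered. Nothing in the document says so. Where preserved performance is discussed, the explanation offered is compensatory effort.

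It can also be said that a condensed article may leave the interval for the between-arm effect to an analysis plan. That is fair: its absence is not the fault raised here. The interval is proposed as the replacement for a statistic that the article does commit to.

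**Conclusion.** The point holds as a reporting and interpretation defect. On the natural reading of sections 2.6 and 3, π adds no information to the p-value and cannot serve the purpose that section 3 gives it. A non-significant result would show at most about 51% for Group x Time (about 50% with N = 48), 51% for a paired test, or 58% for EEG terms with Recording Condition.

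These limits depend only on the degrees of freedom, alpha and the observed-power reading. The spread of the printed value also rests on the planned effect being true and on an assumed pre-post correlation, so it should be quoted with the range over 0.3 to 0.7. No test, error rate, sample size or outcome definition depends on π. The change is worth making, but the validity of the tests does not turn on it.

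**What to change.** Delete π from the results reporting in sections 2.6 and 3, and keep the a priori calculation in section 2.2 as the only power figure. For each outcome, report the between-arm difference in pre-post change with its 95% confidence interval, and interpret the result from that interval. For a null result, state which decrements the interval excludes; this is also what a claim of preserved performance needs.

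If the investigators mean a power other than observed power, section 2.6 should name it and the effect size at which it is evaluated.

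The cost is a change of wording in two sections. The interval comes from the same data and software, with no new measurements and no extra participants.

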##### Selection and justification of EEG channels

2.5.1.1

Electrodes F3, F4, Fz, C3, C4, Cz, P3, P4, Pz, T3, T4, T5, T6, O1, O2, and Oz will be analysed according to the international 10–20 system, allowing comprehensive coverage of the frontal, central, parietal, temporal, and occipital regions. The frontal, central, and parietal regions are particularly sensitive to the effects of mental fatigue, showing increases in theta band power and reductions in alpha band power, phenomena associated with greater attentional effort and decreased cognitive efficiency (19, 61, 62). The temporal and occipital regions were included to ensure a comprehensive characterisation of cortical activity, as previous studies have identified changes in functional connectivity and neural complexity associated with sensory integration and visuospatial regulation under fatigue (62).

Based on explicit theoretical hypotheses, frontal midline electrodes (particularly Fz and adjacent frontal sites) are defined as primary regions of interest (ROIs), given the well-established association between frontal theta activity and mental fatigue. Posterior parietal-occipital regions are included due to their documented involvement in alpha modulation and attentional processing under cognitive load. Analyses focusing on these predefined ROIs and frequency bands (theta, alpha, beta) will be considered primary. Analyses involving additional scalp regions will be clearly identified as exploratory and interpreted with appropriate caution.

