##### VAS

2.5.4.2

The VAS for mental fatigue, applied immediately before and after the cognitive induction task (ST), captures acute fluctuations in the subjective perception of fatigue. This 100 mm continuous scale, anchored between “no fatigue” and “extreme fatigue”, is sensitive to short-term changes induced by cognitive load and task duration (84). Within the experimental group, VAS ratings will be compared pre and post ST to quantify the immediate impact of the intervention on mental fatigue.

In addition, associations between subjective fatigue and other objective markers will be explored. Specifically, post-intervention VAS results will be correlated with EEG spectral characteristics (particularly alpha and theta power), oculomotor parameters (blink rate, pupil diameter, saccadic dynamics, and fixations), and motor performance measures (LSPT and Y-SART). This approach allows us to determine whether higher levels of self-reported fatigue align with neurophysiological and behavioral indicators of reduced performance, providing a multimodal framework for validating the perceptual dimension of fatigue.

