For EEG data (theta, alpha, and beta bands), spectral power within predefined regions of interest (ROIs) will be analyzed using repeated-measures models including Time (pre vs. post mental fatigue) and Recording Condition (eyes open, eyes closed, motor imagery), allowing evaluation of fatigue-related changes across neural states. Primary analyses will focus on frontal midline and posterior ROIs, consistent with the study's theoretical hypotheses. Exploratory analyses across additional scalp regions will be conducted separately and corrected using False Discovery Rate (FDR) procedures to control for multiple comparisons. Correlational analyses (Pearson's r) will explore associations between EEG bands and behavioral performance (LSPT, Y-SART), as well as subjective fatigue scores (VAS and FAS) (94, 95). Topographic maps will be generated to visualize EEG power distributions across cortical regions.

For oculomotor parameters (fixations, saccades, pupil diameter, blink rate), comparisons will assess the impact of mental fatigue on attention dynamics and visual search efficiency. Pearson correlations will explore links between ETS metrics, EEG patterns, and motor performance scores. Eye-tracking outcomes will be interpreted in conjunction with EEG measures, motor performance variables, and subjective fatigue scores, allowing a multimodal framework that reduces interpretative ambiguity.

Motor performance will be analyzed by comparing LSPT and Y-SART results before and after cognitive induction. Metrics such as execution time, technical penalties, and reaction times will be examined to determine whether cognitive fatigue impairs decision-making and technical execution under pressure.

These performance results will be correlated with neurophysiological and oculomotor indicators to investigate predictive relationships. Subjective fatigue will be analyzed using pre and post VAS comparisons and baseline FAS scores. These will be used to triangulate subjective perceptions with objective changes in EEG, ETS, and performance data. Higher self-reported fatigue scores are expected to align with reduced cortical efficiency, altered visual behavior, and degraded motor output.

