To address individual variability, demographic and contextual variables (e.g., age, gender, field position, experience, sleep habits, caffeine intake) will be tested as covariates using ANCOVA or subgroup analyses. This will help determine whether certain profiles exhibit greater resilience or vulnerability to mental fatigue (10, 96).

Finally, multimodal integration will involve constructing correlation matrices and regression models to identify fatigue profiles across domains. This will allow for the identification of converging patterns across the EEG, ETS, motor, and subjective domains, thereby increasing the understanding of the neurocognitive and behavioral effects of mental fatigue. This approach is supported by advanced multivariate methodologies in sports neuroscience and applied psychology (39, 40).

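### The only multiplicity correction covers exploratory EEG regions; the EEG tests called primary, the gaze and motor tests and the correlations have none, and no single primary outcome is named

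*Protocol article*

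**What the plan says.** All points are in the protocol article.

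- **Section 2.6** sets the significance level at 5% for all statistical analyses. Its only multiplicity rule reads: "Exploratory analyses across additional scalp regions will be conducted separately and corrected using False Discovery Rate (FDR) procedures".
- **Primary analyses.** Section 2.5.1.1 says: "Analyses focusing on these predefined ROIs and frequency bands (theta, alpha, beta) will be considered primary". Section 2.6 names the regions: "Primary analyses will focus on frontal midline and posterior ROIs, consistent with the study's theoretical hypotheses". The EEG model has Time and "Recording Condition (eyes open, eyes closed, motor imagery) as within-subject factors, and Group (experimental vs. control) as a between-subject factor".
- **Gaze and motor outcomes.** Section 2.5.2 lists six gaze measures: fixation number and duration, saccade duration and speed, pupil diameter and blink rate. Section 2.5.3 lists three measures from the passing test (LSPT) and two from the agility test (Y-SART). Section 2.6 plans paired t-tests within each group and independent t-tests at each time point.
- **Correlations.** Section 2.6 plans Pearson correlations of EEG with motor and subjective scores, and of gaze with EEG and motor scores. Section 2.5.4.2 adds that "post-intervention VAS results will be correlated with EEG spectral characteristics", and likewise with gaze and motor measures. The last step of section 2.6 is "constructing correlation matrices and regression models to identify fatigue profiles across domains".
- **Outcome hierarchy.** Section 2.5 presents the EEG, gaze, motor and subjective outcomes side by side. The sample size in section 2.2 (34, 17 per group) is tied to none of them.

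**The concern.** The correction is placed where the claims are weakest. The additional scalp regions are already marked as exploratory and to be read with caution, yet they alone are corrected. The tests meant to carry the conclusions are not.

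The word primary is used only within EEG and covers a family of tests with no rule for reading that family. The study's stated subject is football performance, and no test in that domain is singled out. Among several regions, bands, gaze measures and motor scores, the article does not say which result decides the matter.

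The correlations matter too, because the article attaches more than description to them. Sections 2.5.1.2 and 2.6 look for predictors of performance, and section 2.5.6 expects composite markers that could inform athlete monitoring. Markers chosen from a large uncorrected matrix at n = 34 may include chance findings. If raw post-intervention values from both arms are pooled, some correlations may reflect only the difference between arms.

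**Working it through.** **1. The plan's own figure.** Inputs from section 2.2: f = 0.25, alpha 0.05, power 80%, two groups, two times. The correlation between repeated measures is not stated; 0.5 is assumed. For Group x Time, the noncentrality is f² x N x m / (1 - rho) = 0.0625 x 34 x 2 / 0.5 = 8.5, with 1 and 32 degrees of freedom. The critical F is 4.15 and power is 0.807, so N = 34 reproduces. At other assumed correlations the required N is 46 (0.3), 22 (0.7) or 16 (0.8). The figure serves one test at 5%. (Table 1 gives 24 men and 24 women. That is a separate inconsistency; 34 is used here.)

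**2. Primary EEG family.** 2 region sets x 3 bands = 6 Group x Time tests. Each model also has a Group x Time x Condition test, so six is a minimum. Under the null with independent tests, the chance of at least one false positive is 1 - 0.95^6 = 0.265. With equicorrelated test statistics (simulation; correlations assumed):

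| Inter-test correlation | Chance of at least one false positive |
|---|---|
| 0 | 26.5% |
| 0.3 | 23.9% |
| 0.5 | 20.7% |
| 0.8 | 13.8% |

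**3. Power if all six stay primary.** Bonferroni gives alpha = 0.05 / 6 = 0.00833. Under the assumptions of step 1, power at N = 34 falls from 0.807 to 0.547, and 80% power needs N = 54.

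**4. Number of correlations.** The article gives no count. Let e be the number of EEG variables. The pairs in section 2.6 are EEG with 5 motor scores, VAS and FAS (7e), gaze with EEG (6e) and gaze with motor (6 x 5 = 30), in total 13e + 30. Section 2.5.4.2 adds post-intervention VAS with 6 gaze and 5 motor measures (11). Counts are per time point.

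| EEG variables (assumption) | Section 2.6 pairs | With VAS pairs | Expected below 0.05 by chance |
|---|---|---|---|
| 3 (bands only) | 69 | 80 | 3.5 to 4.0 |
| 6 (band x region) | 108 | 119 | 5.4 to 6.0 |
| 18 (band x region x condition) | 264 | 275 | 13.2 to 13.8 |

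The expected counts are 0.05 times the number of pairs and do not depend on independence.

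**5. Correlations across arms.** Suppose two post-intervention measures are uncorrelated within each arm, but the arms differ by d1 and d2 within-arm SDs. With equal arms the pooled correlation is (d1 x d2 / 4) / sqrt[(1 + d1²/4)(1 + d2²/4)]. For d1 = 2 and d2 = 1 this is 0.5 / sqrt(2 x 1.25) = 0.316. The shifts are assumptions. Simulated rates of p < 0.05 with 17 per arm:

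| Shifts (SD) | Rate of p < 0.05 |
|---|---|
| 0.5 and 0.5 | 6% |
| 1.0 and 0.5 | 9% |
| 2.0 and 0.5 | 17% |
| 1.0 and 1.0 | 21% |
| 2.0 and 1.0 | 47% |

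**The case against.** **Multiplicity rules are often left to an analysis plan, and a general 5% level does not rule out adjustment.** This is fair as far as it goes, since the same level also governs the FDR-corrected tests. But the article is not silent. It takes up multiplicity and assigns correction to one set of analyses. Extending it would change the stated scope.

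**The hypothesis is a conjunction.** A reader might infer that any significant measure in any modality would count as support. The documents do not say so. The introduction states the hypothesis in four parts joined together (subjective fatigue, EEG, gaze, performance), and several sections say the modalities will be interpreted jointly. Requiring all four does not inflate error in the way an any-one rule would. What remains is that no rule says which test decides each part.

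**Counting all outcomes overstates the risk.** With 6 EEG, 6 gaze, 5 motor and 1 VAS outcome, 1 - 0.95^18 = 60%. This is an upper bound of limited use. It assumes independence, although the LSPT adjusted score is built from time and penalties, and it includes the VAS, which works mainly as a check that fatigue was induced.

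**The correlations are described as exploring associations, and their number is not stated.** Both points stand. A flat claim of more than a hundred would fail if bands are not split by region. The predictive aims elsewhere in the article only partly offset the exploratory wording.

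**Pooling of arms is not stated.** Correct. Section 2.5.4.2 specifies post-intervention VAS but not which participants enter, and its preceding sentence concerns the experimental group. The 47% is the top of an assumed range and cannot be presented as the expected error rate.

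**Conclusion.** The point holds in limited form. The article corrects only analyses already labelled exploratory. It states no error control for the primary EEG family, the gaze and motor tests or the correlations, and names no single trial-level primary outcome. For the six primary EEG tests the chance of a false positive is about 14% to 26.5%, depending on an assumed inter-test correlation, against a nominal 5%. About 3 to 14 chance correlations are expected, depending on how EEG variables are defined. Bias from pooling arms is conditional: it arises only if both arms enter unadjusted, and the resulting rate runs from about 6% to 47% over the assumed shifts.

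Two stronger readings are not supported: that one significant measure anywhere would confirm the hypothesis, and that the LSPT must replace the EEG analyses as primary. No section ranks one above the other. The sample-size arithmetic is not at fault; it reproduces for one test at 5%, assuming a repeated-measures correlation of 0.5.

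**What to change.** 1. Name one primary test at 5%, two-sided. The choice is the sponsor's, for example Group x Time for frontal-midline theta or the baseline-adjusted group difference in LSPT adjusted score. One test keeps the basis for N = 34.
2. Treat the VAS as the manipulation check.
3. Apply the FDR procedure already planned to the remaining primary region-by-band, gaze and motor tests.
4. Apply FDR separately to the whole correlation matrix. State beforehand how EEG variables enter (by band, region and recording condition), so that its size is fixed.
5. Compute correlations on pre-post change with group partialled out. The FAS is measured only at baseline, so use its baseline score. FDR alone would not remove a correlation created by the difference between arms.

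The cost is wording and a little analysis time. The abstract says no data are available yet, and section 2.1 says registration is still to come, so the change can be made now. The downside is some loss of nominal power for the secondary measures.
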